## Abstract

**Background:**

Tocotrienol, a naturally occurring form of vitamin E, has been extensively studied for its potent antioxidant, anti-inflammatory, and immune-stimulating properties. However, the clinical impact of tocotrienol supplementation on older adults’ overall health and well-being remains relatively unexplored. This research aims to investigate the efficacy of tocotrienol-rich fraction (TRF) on various health parameters associated with general well-being in individuals aged between 50 years and 75 years.

**Objective:**

It is hypothesized that TRF supplementation may exhibit positive outcomes on blood biochemistry and several physiological aspects, including lowered levels of oxidative stress and inflammation biomarkers; improvement in vascular age; and enhancement of skin condition, bone mineral density, and cognitive function.

**Methods:**

This randomized, double-blind, placebo-controlled trial was designed to investigate the effectiveness of TRF supplementation on overall health in healthy older adults. The study aims to assess the impact of a daily dosage of 200 mg of TRF over a period of 6 months. A total of 220 participants is enrolled in the study, with one-half receiving the placebo and the other one-half receiving TRF supplementation. The study comprises 3 time points: baseline, 3 months, and 6 months. At each time point, various measurements are taken to evaluate different aspects of health. The primary outcome measurements include blood biochemistry assessments, such as liver function tests, renal profile, lipid profile, and full blood count. Oxidative stress markers, including malondialdehyde, advanced glycation end products, protein carbonyl, and isoprostane, are also evaluated. Immune response markers such as interleukin-6 and tumor necrosis factor-α are assessed. Satiety regulation is examined through measurements of leptin and ghrelin. Body composition and skin health parameters, including wrinkling, pigmentation, elasticity, hydration, and sebum secretion, are evaluated. Additionally, arterial stiffness is assessed using arteriography at baseline and 6 months. For secondary outcome measures, bone mineral density is measured using dual x-ray absorptiometry, and cognitive function is assessed using the Montreal Cognitive Assessment, Rey Auditory Verbal Learning Test, and digital span test. Both bone mineral density and cognitive function are also measured at baseline and 6 months.

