### Outcomes

The study outcomes are divided into primary and secondary end points. The primary end points include vascular health (arterial stiffness), blood biochemistry (liver function, lipid profile, renal function, full blood count, and fasting glucose), oxidative stress (F2-IsoPs, MDA, AGEs, and PC), inflammation markers (TNF-α and IL-6), appetite regulation (ghrelin and leptin), and skin assessment (elasticity, hydration, transepidermal water loss, pigmentation, sebum secretion, wrinkles, and roughness). Meanwhile, cognitive function (Montreal Cognitive Assessment [MoCA], Rey Auditory Verbal Learning Test [RAVLT], and digit span test) and bone density fall under the secondary outcome measures.

The study encompasses a multifaceted array of assessments and procedures (Figure 1). For primary outcome measures, blood samples (15 mL) are collected as baseline samples for blood biochemistry analyses. Venous blood samples are drawn from the antecubital vein between 8 AM and 10 AM, following an 8- to 10-hour overnight fast. The standardized timing and fasting procedure are followed throughout all study visits (baseline, 3 months, and 6 months) to reduce biological variability caused by circadian rhythms and postprandial effects. After at least 5 minutes of rest to stabilize hemodynamic parameters before sampling, participants are seated, and blood is collected using sterile procedures.

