### Recruitment

The selection of potential trial participants is conducted by the PI based on the inclusion and exclusion criteria. Participants who fail to meet the inclusion and exclusion criteria are defined as screening failures. The PI maintains a Screening Log, which includes screen failures to ensure a systematic selection of participants. Informed consent is obtained from each participant by the contract research assistants. During enrollment, general information (name, gender, age, address, and contact information) is obtained. To ensure security and confidentiality, each participant is assigned a participant-specific code. The code is used to label the participant’s laboratory results. Each participant is reimbursed for standard transportation fees.

Participants are free to withdraw from the study at any time for any reason. Participants may also be withdrawn at any time at the discretion of the PI. Possible reasons for withdrawal include abnormal laboratory values, protocol violation, the participant requiring the use of an unacceptable concomitant medication, participant not complying with protocol procedures, participant developing a condition during the study that violates the inclusion or exclusion criteria, loss to follow-up, death, or any other reason in the PI’s opinion that would impede participation in the study.

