### Analyses

Statistical analysis is conducted using SPSS (IBM Corp). The Kolmogorov-Smirnov test will be performed to assess the normality of the data distribution. Type III sum of squares is set to evaluate the hypotheses.

A mixed-design ANOVA will be used to determine whether supplementation affects the blood biochemistry parameters (inflammation and oxidative stress) and physical health (body composition, skin, cognitive function, and vascular health) at baseline, 3 months, and 6 months among the groups. The Mauchly test of sphericity will be conducted to assess homogeneity of variance and compare the means of the supplemented group with those of the placebo group. To account for the risk of a Type I error as a result of many primary and secondary outcomes, multiplicity correction procedures will be used. In particular, the Benjamini-Hochberg approach for false discovery rate control will be used in each outcome domain (eg, oxidative stress markers, inflammatory markers, cognitive tests). Statistical power and Type I error control are balanced for exploratory research in this method with connected variables. The Tukey post hoc test will be used for comparisons between groups, while the Dunnett test will be used for comparisons within groups over time. In terms of missing data, linear mixed-effects models with the missing at random assumption will be used, which is acceptable given the repeated-measures design and inclusion of observed predictors. Nevertheless, dropout rates in older adult groups might differ from missing at random (for example, because of undetected health decline). To evaluate the possible impact of data missing not at random, sensitivity analyses will be conducted using pattern-mixture models and multiple imputation with delta-adjustment scenarios. These methods aid with determining the robustness of the findings under alternate missingness assumptions. All data will be presented as mean (SD), with statistical significance defined as *P*<.05.

This study requires a total of 220 volunteers as calculated using the power and sample size program. In the case where any participant withdraws or is eliminated during the course of the project, their ID number is not reused. Instead, new volunteers are recruited to maintain the total sample size at 220. The distribution of the IP numbers is rerandomized and adjusted as needed to ensure that both groups remain equally balanced, with 110 participants receiving each IP.

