On average, the screening process typically lasts around 2 hours. According to the latest data, approximately 60% of the volunteers successfully met the inclusion criteria and became eligible for recruitment into the study. The primary reasons for volunteer exclusions were elevated levels of total cholesterol, low-density lipoprotein cholesterol, fasting blood glucose, and blood pressure. On average, each participant requires approximately 3 hours to complete all assessments, excluding blood tests. To accommodate the fasting requirement for blood withdrawal and arterial stiffness assessment, these tests are conducted first. Subsequently, the remaining assessments are performed simultaneously at different stations, allowing participants to visit any available station. To minimize the waiting time, a maximum of 5 participants are scheduled per sampling day. This ensures that participants do not experience prolonged waiting periods.

Throughout the treatment period, the research assistants monitor the compliance of the participants through regular phone calls and short messages. However, the effectiveness of this monitoring method relies on the participants’ availability to respond to or read the messages. Noncompliant cases were primarily attributed to participants’ difficulty with remembering to take the supplement, which is evident when they return the bottles with a higher number of remaining softgels than expected during the 3- and 6-month visits. The data from noncompliant participants are still analyzed. However, it is specifically noted in the CRF so that any potential outliers in data analysis can be identified later.

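### Participants may be withdrawn from the study for abnormal laboratory values, which are primary endpoints, so missing month-6 data can depend on the outcome

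*Protocol article*

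**What the plan says.** The Abstract states: "The primary outcome measurements include blood biochemistry assessments, such as liver function tests, renal profile, lipid profile, and full blood count". The Outcomes section confirms it in the formal list of primary end points, which includes "blood biochemistry (liver function, lipid profile, renal function, full blood count, and fasting glucose". Table 1 schedules these tests at 0, 3 and 6 months. Arterial stiffness is also primary, but it is measured only at 0 and 6 months, as are bone density and cognition (both secondary).

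The Recruitment section says: "Participants may also be withdrawn at any time at the discretion of the PI". It continues: "Possible reasons for withdrawal include abnormal laboratory values, protocol violation, the participant requiring the use of an unacceptable concomitant medication". A further listed reason is "participant developing a condition during the study that violates the inclusion or exclusion criteria". No analyte, limit or grade is attached. The text speaks of withdrawal from the study, not only from the supplement.

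The Analyses section adds that after a withdrawal "new volunteers are recruited to maintain the total sample size at 220". It names a mixed-design ANOVA for the treatment comparison, linear mixed-effects models under missing at random (MAR) for missing data, and pattern-mixture and delta-adjusted imputation analyses for departures from MAR. The primary analysis is by intention to treat in all randomized participants. A per-protocol analysis of completers is secondary.

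**The concern.** A participant whose month-3 liver, lipid, renal, blood-count or glucose result is judged abnormal can be taken out of the study because of the very quantity the trial compares, and then has no month-6 value. If the supplement shifts these results, the two arms lose different numbers and different kinds of people. Where TRF lowers LDL, more placebo than TRF participants would cross any given limit, and the observed month-6 difference would shrink. Where TRF harmed a few people, their later course would go unobserved. Replacing those withdrawn restores the head count but not the lost outcomes.

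**Working it through.** The plan gives no figure for this effect, so there is none to reproduce. The check has three parts.

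**1. Can a primary result remove someone before month 6?** Yes. Biochemistry is primary and measured at month 3 (Outcomes, Table 1). Abnormal laboratory values are a listed reason for withdrawal (Recruitment). No section describes measurement after withdrawal.

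**2. How large is the effect on LDL, and in which analysis?**

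Inputs from the Sample Size section: difference 3.11 − 2.66 = 0.45; common SD √((0.81² + 1.25²)/2) = 1.053.

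Assumptions: the correlation between visits is 0.5 to 0.8; the cut-off is such that 5, 10 or 20% of placebo exceed it at month 3; everyone above it is withdrawn; the true effect is −0.45 at months 3 and 6. There were 400,000 simulated participants per arm. Selected results for the month-6 difference:

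| Correlation | Withdrawn, placebo / TRF | All participants | Completers only | MAR, month-3 value kept | MAR, trigger outside the data |
|---|---|---|---|---|---|
| 0.5 | 5% / 1.9% | −0.446 | −0.414 | −0.446 | −0.405 |
| 0.5 | 20% / 10.3% | −0.447 | −0.368 | −0.447 | −0.338 |
| 0.7 | 10% / 4.3% | −0.452 | −0.379 | −0.452 | −0.404 |
| 0.8 | 20% / 10.2% | −0.445 | −0.317 | −0.447 | −0.385 |

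The withdrawal percentages refer to the month-3 trigger. In the last column the trigger is instead an unscheduled result close to month 6, modelled as the month-6 value plus noise, with the same share of placebo withdrawn.

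- Completers only: attenuation runs from 1 − 0.414/0.446 = 7% to 1 − 0.317/0.445 = 29%.
- MAR with the month-3 value kept: no attenuation, because withdrawal then depends only on recorded data.
- MAR with the trigger outside the data: the estimate lies between −0.43 and −0.34 across all settings.
- No true effect: every estimate stays within 0.005 of zero.

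Power follows from Φ(δ/(σ√(2/n)) − 1.96). With σ = 1.053 and n = 93 per group, σ√(2/n) = 0.154. For δ = 0.45 power is 0.83; for 0.414 it is 0.76; for 0.317 it is 0.54. The SD and n are held fixed, so these values are only illustrative.

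A second set of assumptions was also run: LDL mean 3.0, SD 0.8, correlation 0.6 to 0.8, screened below 4.1, withdrawal above 3.4, 3.8 or 4.1 at month 3, effect 0.2 or 0.45. It withdraws 4 to 27% of placebo and 1 to 19% of TRF. The month-6 difference in level among completers is then 0.65 to 0.92 of the truth, an attenuation of 8 to 35%. The month-6 change from baseline among completers keeps a ratio of 0.99 to 1.00. The reason is that when baseline and month 6 are equally correlated with month 3, selection on month 3 leaves their difference almost untouched. The month-3 change among completers is not spared: it loses from about 3% up to about a fifth.

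**3. What about outcomes without a month-3 value?** Someone withdrawn after month 3 has only a baseline arterial stiffness value. A model of stiffness alone does not contain the laboratory result that caused the withdrawal, so MAR given the modelled data need not hold. Bias arises if that result is related to month-6 stiffness given arm and baseline. If it is not, the loss is one of precision only. The documents give no figure from which to size this.

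**The case against.** A reader might infer that the month-6 biochemistry comparison is made in people selected for staying normal. The documents do not support that.

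- **Planned handling.** All randomized participants enter the primary analysis, a mixed model under MAR is planned for missing data, and sensitivity analyses cover departures from MAR. A month-3 trigger is itself a recorded outcome, which is the case MAR handles.
- **Discretion.** Withdrawal is optional and has no stated threshold; the simulations make it automatic. Of 211 recruited, 167 had completed (Results), so 44 (21%) had not, for any reason and including people possibly still in follow-up. Withdrawing 27% of placebo on LDL alone is therefore an extreme case. The number actually withdrawn for laboratory values is not given.
- **Harm.** Abnormal month-3 values stay in the month-3 comparison and in the mixed model, so a harm would not vanish. Only its later course would be unobserved.
- **Entry criteria.** Eligibility names satisfactory liver and renal tests, not lipid limits. The Discussion remark "The primary reasons for volunteer exclusions were elevated levels of total cholesterol, low-density lipoprotein cholesterol, fasting blood glucose, and blood pressure" describes screening, not withdrawal during the study.
- **Condensed article.** A fuller protocol may provide for follow-up after withdrawal.

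These points stand, and they confine the problem. They do not remove it. The article states a rule of outcome-related withdrawal from the study, with replacement to hold 220, and this sits badly with an analysis of everyone randomized. It names both an ANOVA, which conventionally uses only people with every visit, and a mixed model, without saying which is primary. Sensitivity analyses probe assumptions; they do not supply values that could have been measured.

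**Conclusion.** The point holds in limited form. The withdrawal rule allows month-6 data to go missing because of a primary outcome, and differently by arm. For biochemistry, the mixed model that keeps the month-3 value largely corrects this. Exposure remains in a complete-case ANOVA, in the per-protocol analysis, for triggers outside the analysis data, and for outcomes measured only at 0 and 6 months.

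The 7 to 35% attenuation applies to the month-6 difference in level among completers, under assumed cut-offs, correlations and automatic withdrawal. It should not be read as the bias of the planned MAR analysis. Nor does the rule create a false effect: with no treatment effect, no difference appeared in the simulations. The change is worth making because this missingness is avoidable at little cost.

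**What to change.** In Recruitment, separate the decision to stop the supplement, which stays with the principal investigator unchanged, from the end of study participation. State that participants affected by an abnormal laboratory value, or by a new condition that breaches the entry criteria, attend the remaining scheduled visits unless they withdraw consent, die or are lost to follow-up.

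Keep the triggering laboratory value in the dataset, including results from unscheduled tests. In Analyses, name the linear mixed model on all randomized participants as the primary analysis, with replacements counted in addition to those they replace. Report the number withdrawn for laboratory values by arm, including those already withdrawn, and retain their month-3 values.

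The cost is an amended paragraph and a few visits that were already scheduled, which some participants may decline. The reach is limited: 211 of 220 are recruited and 167 have completed. For earlier withdrawals, only retaining the data and reporting the counts is still possible.

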**Results:**

The study is progressing as planned, with 209 participants recruited as of April 2025. The research was funded in 2019, and data collection started in December 2020. Preliminary data analysis has been completed for the first 120 participants, and final results are expected upon completion of data collection and unblinding in 2026.

**Conclusions:**

By comprehensively evaluating these health aspects, this study seeks to provide valuable insights into the potential benefits of tocotrienol supplementation for promoting the overall health and well-being of the aging population.

**Trial Registration:**

National Medical Research Register (NMRR) NMRR-19-2972-51179; https://tinyurl.com/yy9yueer

**International Registered Report Identifier (IRRID):**

DERR1-10.2196/73039

## Introduction

### Background

Aging is a progressive process characterized by the gradual loss of tissue and organ function over time [1]. Two theories of aging include the free radical theory of aging, which later evolved into the oxidative stress theory of aging, and a theory based on low-grade inflammation, or inflammaging, in older adults. The oxidative stress theory of aging is based on the hypothesis that age-related functional declines occur as a result of the accumulation of oxidative damage to macromolecules such as lipids, DNA, and proteins caused by reactive oxygen and nitrogen species (RONS) buildup [2]. With advancing age, the accumulation of RONS leads to post-transcriptional modifications and oxidative damage, often contributed to by elevated levels of oxidative stress biomarkers including advanced glycation end products (AGEs), malondialdehyde (MDA), protein carbonyl (PC), and F2-isoprostanes (F2-IsoPs) [3]. In parallel, chronic low-grade inflammation has been linked to the onset of age-related chronic diseases such as cardiovascular disease, diabetes, and cancer [4]. In older adults, there is often an imbalance between excessive free radicals and low antioxidant levels, along with increased risk of chronic inflammation due to elevated inflammatory cytokine production, which may lead to disruption in normal cellular physiology [5,6]. High levels of oxidative stress biomarkers and inflammatory cytokines are associated with low cognitive performance, osteoporosis, atherosclerotic characteristics, skin conditions, and renal problems in older adults [7-9].

According to the Department of Statistics, Malaysia is officially regarded as an aging nation, as individuals aged 65 years and older were predicted to make up 7.7% of the population as of 2024 [10]. This indicates an urgent need to identify preventive, nonpharmacological strategies for maintaining the health and well-being of the older adult population. Introducing natural adjuncts like tocotrienol-rich fraction (TRF) supplementation may serve as a cost-effective and physiologically beneficial approach to reducing the health care burden associated with aging while potentially supporting healthy aging and improving overall quality of life for older adults.

Tocotrienol is a naturally occurring vitamin E that is predominantly found in palm oil [11]. It can be further distinguished into 4 isomeric forms (α, β, γ, and δ), depending on the location and number of methyl groups on the chromanol ring. Tocotrienols, as opposed to tocopherols, have unsaturated isoprenoid side chains with 3 double bonds, allowing for greater cellular penetration and dispersion inside lipid membranes [6,12]. This structural difference improves their antioxidant and anti-inflammatory properties. Cumulative scientific evidence has convincingly shown that tocotrienol possesses pronounced antioxidative function by effectively neutralizing free radicals, including RONS, which ultimately reduces oxidative stress [11,13-22]. Tocotrienol also possesses anti-inflammatory properties by ameliorating inflammatory markers that are consistently associated with age-related chronic diseases and disability [4], including interleukin-6 (IL-6), tumor necrosis factor-alpha (TNF-α), and C-reactive protein (CRP) [23-25]. IL-6 is a pleiotropic cytokine produced by the immune cells, vascular endothelial cells, adipocytes, and skeletal muscle and possesses both anti-inflammatory and pro-inflammatory properties [26]. TNF-α, another cytokine, is mainly produced by macrophages and other cell types in response to cell damage [27], while CRP is an acute-phase protein produced by the liver in response to elevated IL-6 and TNF-α levels [28-30]. These properties render tocotrienol an attractive therapeutic candidate for slowing down the aging process and thus potentially extending the lifespan of older adults [11,13].

Moreover, tocotrienol also modulates inflammation by targeting crucial transcription factors such as nuclear factor kappa B (NF-κB), the signal transducer and activator of the transcription-3 (STAT-3) pathway, and other cytokine regulators integral to the inflammatory signaling cascade [12,13,22,31-33]. Tocotrienols have been shown to exhibit isoform-specific effects on anti-inflammatory potency. For instance, several studies have demonstrated that δ-tocotrienol exhibited the most potent inhibitory effect on IL-6 and TNF-α production as compared with other isoforms [24,34]. Another study has shown that δ-tocotrienol inhibits TNF-α–induced NF-κB activation caused by upregulation of the anti-inflammatory protein A20 [35]. In addition, Muid et al [32] demonstrated that both δ- and γ-tocotrienols have higher potency in inhibiting IL-6 production and NF-κB activation than α- and β-tocotrienols in lipopolysaccharide-stimulated human umbilical vein endothelial cells. The NF-κB pathway inhibition induced by γ-tocotrienol also contributes to downregulation of oncogenic gene expression, thus promoting tumor cell apoptosis, which is crucial for suppressing tumor metastasis [36]. Moreover, combined treatment with γ-tocotrienol and an epidermal growth factor receptor inhibitor showed suppression in epidermal growth factor–dependent STAT-3 signaling in mammary tumor cells [37]. Collectively, these findings underscore the pivotal role of tocotrienols in modulating inflammation through multifaceted inhibition of key transcription factors, suppression of pro-inflammatory cytokines, and regulation of signaling pathways central to the inflammatory cascade. This positions tocotrienols as promising agents for the prevention and management of inflammation-driven diseases, including cancer and chronic inflammatory conditions.

Furthermore, these scientific investigations have illuminated tocotrienols’ ability to enhance skin health through UV protection and skin-lightening effects, both in preclinical and clinical models [38-42]. Tocotrienols have also demonstrated their potential for improving lipid profiles among individuals with dyslipidemia and hypertension [12,43-48] and have been shown to regulate leptin expression, thereby influencing appetite control and energy homeostasis [49-54]. To date, no study has specifically investigated the effect of tocotrienols on ghrelin expression. Therefore, our study aims to fill this knowledge gap and provide novel insights into this unexplored area.

In bone health, tocotrienols promote osteoblast survival and proliferation through free radical protection and inhibit osteoclasts by downregulating the mevalonate pathway. They also regulate gene expression to promote bone formation [55-66]. Similarly, tocotrienols positively influence neurological health by modulating gene expression in the brain, potentially enhancing memory and motor function while delaying Alzheimer disease progression. Notably, α-tocotrienol at nanomolar concentrations has been shown to attenuate enzymatic and nonenzymatic mediators of arachidonic acid metabolism and neurodegeneration [11,67-71].

TRF is a commercial mixture of vitamin E isomers, containing approximately equal proportions of α-tocopherol (αTP) and α-, β-, γ-, and δ-tocotrienol isomers. TRF supplement with a complete spectrum of tocotrienol isomers has been found to alleviate inflammatory symptoms of allergic rhinitis [72], enhance mental health and cognition [73], reduce inflammation and oxidative stress in ulcerative colitis [31], and mitigate UV-induced skin inflammation [38]. A previous study reported that TRF can improve antioxidant enzyme activities and glutathione levels in women aged between 50 years and 55 years [74]. In the same study, TRF supplementation was found to reduce MDA levels as early as 3 months, while oxidative damage toward DNA was reduced in women after 6 months of supplementation [75]. Furthermore, related isomers derived from the same source have demonstrated benefits in cardiovascular, liver, and metabolic functions [12,76] while exhibiting inhibitory effects on the growth of gastric cancer [77], prostate cancer [78], and breast cancer [79]. The findings from these studies provide a compelling basis to initiate a clinical trial aimed at evaluating the impact of TRF on the well-being of healthy individuals.

